## Abstract

**Background:**

Suicide is among the top 10 leading causes of death worldwide. Of people who died by suicide, the majority are diagnosed with depression. It is estimated that 25%-60% of people with bipolar depression (BD) will attempt suicide at least once, and 10%-15% will die by suicide. Several treatments, such as lithium, clozapine, electroconvulsive therapy, and cognitive behavioral therapy, have been shown to be effective in treating suicidality. However, these treatments can be difficult to tolerate or may take months to take effect. Ketamine, a glutamate N-methyl-D-aspartate antagonist, has been shown to have rapid antisuicidal effect and antidepressant qualities, and is thus a promising intervention to target acute suicidality in patients with BD. However, the biological mechanism underlying its therapeutic action remains poorly understood. Enhancing our understanding of underlying mechanisms of action for ketamine’s effectiveness in reducing suicidality is critical to establishing biological markers of treatment response and developing tailored, personalized interventions for patients with BD.

**Objective:**

This is an open-label clinical trial to test the safety and feasibility of repeated ketamine infusions to treat acute suicidality. The primary objective is to test the safety and feasibility of ketamine intervention. The secondary objective is to examine ketamine’s potential neurophysiological mechanisms of action by assessing cortical excitation and inhibition to determine potential biomarkers of clinical response. Other objectives are to evaluate the effect of ketamine on acute suicidality and other clinical outcomes, such as depressive symptoms and quality of life, to inform a future larger trial.

**Methods:**

This open-label clinical trial aims to test the safety and feasibility of repeated ketamine infusions in patients with BD for suicidality and to assess ketamine’s neurophysiological effects. A sterile form of racemic ketamine hydrochloride will be administered over a 40-minute intravenous infusion 2 times per week on nonconsecutive days for 4 weeks (8 sessions). We will recruit 30 adults (24-65 year olds) over 2 years from an academic psychiatric hospital in Toronto, Canada.

**Results:**

This study is currently ongoing and actively recruiting participants. So far, 5 participants have completed the trial, 1 is currently in active treatment, and 8 participants are on the waitlist to be screened. We anticipate initial results being available in the fall of 2023. This proposal was presented as a poster presentation at the Research to Reality Global Summit on Psychedelic-Assisted Therapies and Medicine, held in May 2022 in Toronto, Canada.

**Conclusions:**

Developing effective interventions for acute suicidality in high-risk populations such as those with BD remains a major therapeutic challenge. Ketamine is a promising treatment due to its rapid antidepressant and antisuicidal effects, but its underlying neurophysiological mechanisms of action remain unknown.

**Trial Registration:**

ClinicalTrials.gov NCT05177146; https://clinicaltrials.gov/ct2/show/NCT05177146

**International Registered Report Identifier (IRRID):**

DERR1-10.2196/41013

## Introduction

### Background and Rationale

Suicide is among the top 10 leading causes of death, with progressively increasing rates and is a critical public health issue [1]. Bipolar depression (BD) is a serious psychiatric condition with a high mortality rate due to suicide [2]. Between 25% and 60% of those with BD will attempt suicide at least once, and 10%-15% will die by suicide [3-5]. Several interventions, such as lithium, clozapine, electroconvulsive therapy, and cognitive behavioral therapy, have demonstrated antisuicidal properties [4,5]. However, as polypharmacy is common in patients with bipolar illness [6], adding another treatment can be difficult to tolerate, or new treatments may take months to take effect. Therefore, there is an urgent need to develop robust interventions to treat suicidality in patients with BD rapidly. In addition, establishing biological markers of treatment response is critical in developing personalized, tailored treatment interventions.

A paradigm shift from a monoamine hypothesis to a plasticity-based hypothesis of depression represents a substantial advancement, where accumulating evidence suggests that glutamatergic or excitatory neurotransmission system dysfunction plays a pivotal role in depression [7-9]. There are 3 classes of glutamate-gated ion channels such as α-amino-3-hydroxy-5-methyl-4-isoxazole propionic acid, and kainite and *N*-methyl-d-aspartate (NMDA) receptors that transduce the postsynaptic signal [7]. NMDA receptors are distributed throughout the brain and are fundamental to excitatory neurotransmission and the normal functioning of the central nervous system (CNS) [7,8]. Ketamine is the first clinically used NMDA receptor antagonist with a primary mechanism of action closely linked to the blockade of the NMDA receptor at the phencyclidine site, which mediates excitatory synaptic transmission through the CNS [8-10].

Developing effective interventions for acute suicidality in high-risk populations, such as BD, remains a major therapeutic challenge. Ketamine is a promising treatment modality due to its rapid antisuicidal [11,12] and antidepressant [13] effects, with numerous studies demonstrating its safety and efficacy in subanesthetic doses administered over 40-minute intravenous (IV) infusions [11-13]. Despite growing interest in ketamine interventions in depressive disorders, our understanding of ketamine’s underlying neurophysiological mechanisms of action, especially concerning suicidality, remains very limited.

Noninvasive brain stimulation neurophysiological tools, such as transcranial magnetic stimulation (TMS), offer an opportunity to study human brain cortical physiology mechanisms in vivo with high temporal resolution [14]. The combination of TMS with a CNS pharmacological agent, such as ketamine, will provide a platform to explore the neurophysiological basis of the impact of ketamine on brain physiology, an important piece of work toward identifying neurobiomarkers of treatment response. Until present, only some studies have attempted to examine the excitatory and inhibitory circuits by using a range of TMS protocols during infusion of incremental doses of ketamine [15-17], primarily using very low ketamine doses or single doses in healthy volunteers. Currently, the prediction of the therapeutic response in those with mood disorders as measured by changes in cortical excitability continues to be in very early stages and has not been systematically tested, making this proposal uniquely positioned among other neurophysiological studies on ketamine and TMS. Our group has previously demonstrated impaired GABA (gamma-aminobutyric acid) inhibition from the motor cortex in patients with depression, a finding that was most pronounced in patients with treatment-resistant depression [16,18,19]. In addition, Croarkin et al [19] demonstrated impaired NMDA receptor–mediated excitation in depression.

### Objectives

The primary objective of this open-label pilot clinical trial is to examine the safety and feasibility of repeated subanesthetic doses (0.5-0.8 mg/kg) of ketamine administered over 40-minute IV infusions in patients with BD to treat acute suicidality. The secondary objective is to analyze the potential impact of ketamine on neurophysiological markers associated with cortical excitation and inhibition as a proxy of NMDA receptor activity in the cortex. Our scientific group has successfully applied TMS-electromyography (EMG) and TMS-electroencephalogram (TMS-EEG) paradigms to assess cortical activities in patients with psychiatric issues [15,18]. Thus, we will use these paradigms to investigate the impact of ketamine on cortical activities in patients with BD and suicidality. We have previously reported that intracortical facilitation is abnormal in depression [14,18] and is closely associated with NMDA receptor–mediated neurotransmission [9,18]. This study will evaluate cortical excitation and inhibition pre- and postketamine course in patients with BD and suicidality to determine a biological target of ketamine treatment response. We will use a TMS-EMG paradigm to investigate the impact of ketamine on cortical excitation via intracortical facilitation and cortical inhibition via short-interval cortical inhibition paradigms [19-21]. Next, we will compare the effect of ketamine on resting-state cortical oscillation via EEG. These results will provide important evidence for the role of NMDA receptors in cortical physiology, which may serve as a ketamine biomarker and would be a crucial breakthrough in determining potential predictors of clinical response for suicidality in patients with BD.

### Trial Design

The DEEPP (Anti-suicidal Response to Ketamine in Treatment-Resistant Bipolar Depression) study is designed as an open-label pilot clinical trial to assess (1) the feasibility of a series of IV ketamine infusions to treat suicidality in patients with BD and (2) ketamine’s neurophysiological markers associated with cortical excitation and inhibition.

## Methods

### Study Setting

Potential participants will be recruited from 1 site, specifically the Centre for Addictions and Mental Health, a large academic center located in Toronto, Ontario, Canada, over 2 years.

### Eligibility Criteria

*Inclusion criteria* are patients who (1) meet criteria for bipolar disorder according to DSM-V (Diagnostic and Statistical Manual of Mental Disorders, 5th edition) criteria as confirmed by the Mini-International Neuropsychiatric Interview (MINI) [22]; (2) meet criteria for a current depressive episode, confirmed with the 24-item Hamilton Rating Scale for Depression (HRSD-24) score of 14 and above [23]; (3) experiencing suicidal ideation as defined by a score of 9 or higher on the Scale for Suicide Ideation (SSI) [24,25]; (4) capable of providing consent; (5) outpatients; (6) able to speak and understand English; and (7) aged 24-65 years, inclusive.

*Exclusion criteria* are patients who (1) have a history of a substance use disorder within the past month or a lifetime history of ketamine substance use disorder, as confirmed by the MINI; (2) concomitant major unstable medical illness (eg, poorly controlled hypertension, enlarged prostate, renal- or urinary-related issues, the presence of cardiac decompensation/heart failure, results of liver function tests [alanine transaminase and aspartate transaminase] are 3 times or greater than the upper limit of normal readings); (3) pregnancy or the intention to become pregnant or breastfeeding during the study as confirmed by self-report. Female participants of reproductive potential must be willing to use a medically acceptable method of birth control which includes highly effective (eg, approved hormonal contraceptives, intrauterine device, tubal ligation) or double barrier (eg, male condom with a diaphragm, male condom with cervical cap) methods of contraception or abstinence if that is the usual and preferred lifestyle of the participant; (4) DSM-V diagnosis of any primary psychotic disorder, obsessive-compulsive disorder, posttraumatic stress disorder (current), unipolar depression, other subtypes of depressive disorders, or current psychotic symptoms as confirmed by the MINI; (5) current episode meeting criteria for mania/hypomania or mixed episode as per DSM-V criteria on the MINI or as determined by the study team; (6) primary diagnosis of severe personality disorder as assessed during the initial consultation with a study psychiatrist prior to study entry; (7) any significant neurological disorder (eg, a space occupying brain lesion, a history of stroke, a cerebral aneurysm, a seizure disorder, Parkinson disease, Huntington chorea, multiple sclerosis) as assessed through medical history review during the initial consultation with a study physician prior to study entry; (8) requiring a benzodiazepine with a dose equivalent to lorazepam 2 mg/day or higher; (9) being on any anticonvulsant (eg, lamotrigine, topiramate, carbamazepine) or opioid medication due to the potential of these medications to limit the efficacy of ketamine; (10) cognitive or physical impairment that may potentially interfere with IV ketamine administration or participants’ ability to stay in the same place for a 2-hour monitoring supervision as assessed through medical history review during the initial consultation with a study physician prior to study entry; (11) any intracranial implant (eg, aneurysm clips, shunts, cochlear implants) or any other metal object within or near the head, excluding the mouth, that cannot be safely removed given that we will be using TMS-EMG/EEG; (12) inability to secure escort to accompany them back home after ketamine sessions; or (13) any known allergy to ketamine or any component or ingredient of the ketamine preparation.

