
### Discontinuation Criteria

Participants will be discontinued from the study if they cannot safely continue the study based on any of the following criteria: (1) experience clinically significant worsening of depressive symptoms (50% increase in HRSD-24 scores from baseline on 2 consecutive ratings); (2) require in-patient hospitalization due to the presence of clinically significant suicidal ideation with imminent intent or attempted suicide; (3) develop clinically significant worsening of mood or physical symptoms (assessed by a study physician); (4) miss over 2 consecutive treatments during the study without the cause; (5) develop any medical illness that may be unstable; (6) experience a seizure; (7) become pregnant, or (8) withdraw consent.

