### Recruitment

This is a single-site open-label pilot safety and feasibility study that will be conducted at the CAMH. The CAMH is a large urban academic institution offering psychiatric care to a diverse population across the province. We intend to recruit participants through CAMH General Division Ambulatory services, which annually provides over 500 consultations for mood-related concerns. The study’s PI is a staff psychiatrist and clinician-scientist in General Division who provides outpatient services to a large population with mood disorders at local and provincial levels. PI is also an interventional psychiatrist working as a part of the Therapeutic Brain Intervention Centre, seeing many patients with treatment-resistant and severe mood disorders. She is also US certified in ketamine interventions and a member of the American Society for Ketamine Physicians (ASKP). This study group has extensive experience with recruiting patients for clinical trials as the PI of this study and coinvestigators are clinician-scientists who provide care to a large number of patients with mood disorders within the context of clinical trials. Thus, we believe recruiting 30 participants over 2 years is feasible.

In addition to group expertise, we will utilize a CAMH-wide recruitment strategy, specifically the Clinical Engagement and Research Recruitment (CLEARR) model, where all new referrals to the CAMH clinics are prescreened, and all patients are informed about clinical research at the time of their initial clinical assessment. The study site will make efforts to recruit a representative and ethnically diverse sample. CAMH services a very diverse inner-city population through numerous satellite clinics in several minority neighborhoods throughout the city. Toronto has diverse cultural representation as almost 75% of its population, aged 15 and older, have direct ties to immigration. In this study, we anticipate our recruitment will follow the ethnic distribution of White/non-Hispanic 50%, Asian 20%, Southeast Asian 15%, Black/non-Hispanic 10%, and Hispanic 5%. We also expect that 60% of our population enrolled at the CAMH site will be female based on our prior experience with clinical trials at the CAMH.

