### Data Collection Methods

Data will be collected on a baseline assessment, weekly during the course of IV ketamine, within a week after the completion of the intervention, and following 4 weeks for a final follow-up. Assessments will include psychiatric assessment, physical examination, and clinical assessments through manualized validated clinical scales (Multimedia Appendices 1 and 2).

*Psychiatric assessment* will include a consultation with a study physician to confirm a diagnosis. Demographic information, medical and psychiatric history, and concomitant medications will also be included.

A *physical examination* will include a physical exam performed by a study physician or a delegate, and blood work and electrocardiography for medical clearance according to standard clinical procedures also be reviewed by the study physician. Blood tests will include complete blood count with differential tests (white blood cells, red blood cells, hemoglobin, hematocrit, mean corpuscular volume, mean corpuscular hemoglobin, mean corpuscular hemoglobin concentration, red cell distribution width, mean platelet volume, platelet, nucleated red blood cell count, neutrophil count, lymphocyte count, monocyte count, eosinophil count, basophil count); blood chemistry test, including liver function (alanine transaminase and aspartate transaminase), kidney function (blood urea nitrogen and creatinine), and electrolytes (sodium, potassium, chloride, and phosphate); and thyroid function (thyroid-stimulating hormone). Study participants’ blood pressure will also be monitored before, during, and after treatment.

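### Exclusion 3 confirms pregnancy by self-report and the article mentions no pregnancy test, so the stated method cannot reliably enforce the exclusion

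*Protocol article*

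**What the plan says.** All references are to the Protocol article.

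- **Eligibility Criteria, exclusion 3.** The criterion excludes "pregnancy or the intention to become pregnant or breastfeeding during the study as confirmed by self-report". It continues: "Female participants of reproductive potential must be willing to use a medically acceptable method of birth control", and lists highly effective methods, double-barrier methods or abstinence.
- **Discontinuation Criteria, item 7.** Among the reasons a participant cannot safely continue is to "become pregnant, or (8) withdraw consent". The article gives no means of detecting pregnancy during the course.
- **Data Collection Methods.** The physical examination is accompanied by "blood work and electrocardiography for medical clearance according to standard clinical procedures". The panel is then itemised: "Blood tests will include complete blood count with differential tests", with each blood-count component named; "blood chemistry test, including liver function (alanine transaminase and aspartate transaminase), kidney function (blood urea nitrogen and creatinine), and electrolytes", with the individual electrolytes named; and "thyroid function (thyroid-stimulating hormone". No hCG is listed. The clinical and neurophysiological assessments that follow include no urine or other pregnancy test.
- **Drug Administration and Scheduling.** Two infusions a week for 4 weeks, 8 in total.
- **Recruitment.** The article expects that "60% of our population enrolled at the CAMH site will be female". The target is 30 participants, and the age range is 24 to 65.

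**The concern.** The plan treats pregnancy as a safety boundary at entry and again during treatment, but the method named for checking it at entry depends on what the participant already knows. Someone in early, unrecognised pregnancy can answer truthfully that she is not pregnant and be found eligible.

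The method is also weaker than the plan's own practice for other exclusions. Psychiatric exclusions are confirmed by structured interview, neurological disorder by a physician's review of the history, and liver disease by a laboratory threshold that matches two of the listed blood tests. Pregnancy also has a laboratory test, and blood is drawn for clearance anyway.

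What is at stake is participant safety and the credibility of the eligibility rule, in a trial whose primary objective is safety and feasibility. No endpoint, sample size or analysis is affected.

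**Working it through.** **Step 1. The plan's own figure.** 2 infusions per week × 4 weeks = 8, which matches the stated total. Eight is the most a participant could receive, not the expected exposure.

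**Step 2. What each provision can and cannot do.**

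| Provision | What it does | Detects an unrecognised pregnancy at entry? |
|---|---|---|
| Self-report (exclusion 3) | Captures known pregnancy, intention to conceive, breastfeeding | No |
| Contraception requirement (exclusion 3) | Lowers the chance of conceiving during the trial | No |
| Itemised clearance bloods (Data Collection Methods) | Blood count, liver, kidney, electrolytes, thyroid | No; no hCG listed |
| Discontinuation item 7 | Ends participation once pregnancy is known | No; needs the pregnancy to be recognised first |

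Nothing described in the article closes the gap. The mismatch between criterion and method does not depend on any rate.

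**Step 3. Scale.**

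Inputs from the article: 30 participants and an expected 60% female, so 0.60 × 30 = 18 women. The age range includes women both within and beyond reproductive age.

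Inputs not in the article:
- n, the number of women of reproductive potential. It can lie anywhere from 0 to 18.
- p, the probability that such a woman has an unrecognised pregnancy at screening. I assume 0.5% to 2%, for illustration only.

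Treating women as independent, the chance of at least one case is 1 − (1 − p)^n.

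| n | p = 0.5% | p = 2% |
|---|---|---|
| 0 | 0% | 0% |
| 10 | 1 − 0.995^10 = 4.9% | 1 − 0.98^10 = 18.3% |
| 18 | 1 − 0.995^18 = 8.6% | 1 − 0.98^18 = 30.5% |

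The range the article allows at these rates is 0% to about 30%. The row for 10 women only shows how the result moves with n; the article gives no basis for preferring it. The assumed rates are not adjusted for a group who agree to use contraception and report no intention to conceive, so the upper end may be too high.

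**The case against.** The strongest objection is that this is a condensed article. It refers the assessments to a SPIRIT flowchart and checklist, and it has a consent form as an appendix; none of these is shown. The clearance work-up is said to follow standard clinical procedures, the blood list is not declared exhaustive, and a urine test would not appear in a list of blood tests. A pregnancy test may therefore exist in the full protocol. This stands as a limit on what can be claimed. It does not remove the point, because the article is not silent on the method: it names self-report. If a test exists, exclusion 3 describes the check wrongly; if not, the check is inadequate. The text needs correcting in both cases.

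A second objection is that the self-report phrase closes a list of three items, two of which (intention to conceive and breastfeeding) are naturally established by asking. The wording does not say that self-report is the sole check. That is fair, but the natural reading covers all three items. If the phrase is limited to the last two, pregnancy has no stated method of confirmation at all.

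A reader might infer more than the article supports:

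- **That no step in the trial would ever detect the pregnancy.** The full schedule of assessments is not shown, and the article provides weekly physician follow-up during the course.
- **That an affected participant would receive all eight infusions.** Eight is the ceiling; recognition during the course triggers discontinuation.
- **That the probability can be narrowed, for instance by supposing about half of the 18 women are of reproductive potential.** The article gives neither that share nor a rate of unrecognised pregnancy.
- **That the provisions contradict one another.** Excluding pregnancy, requiring contraception and discontinuing on pregnancy are mutually consistent. The fault is in the method of confirmation.
- **That leaving out how item 7 is ascertained during treatment is itself an error.** An article can leave that detail to the full protocol.

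**Conclusion.** The point holds in this form: the method exclusion 3 names for confirming pregnancy cannot reliably enforce the exclusion, and no pregnancy test appears in the article to make up for it. An unrecognised pregnancy at entry could be exposed to some or all of the 8 infusions before item 7 of the discontinuation criteria applies.

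Confidence is high on what the article says and on the logic, and moderate on trial conduct, because the full protocol and its schedule are not shown. No single probability should be claimed. With 0 to 18 women concerned and an assumed rate of 0.5% to 2%, the chance of at least one case is 0% to about 30%. The correction should be made, as a safety and eligibility matter; it does not threaten the validity of the results.

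**What to change.** In exclusion 3, separate the three items. For participants of reproductive potential, confirm the absence of pregnancy by a negative pregnancy test before the first infusion, for example by adding hCG to the clearance blood sample and to the list of tests in Data Collection Methods. Keep self-report for intention to conceive and breastfeeding. If the full protocol already contains a test, reword exclusion 3 to agree with it.

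The article does not date the clearance sample relative to the first infusion, so the amended text should say when the test is done.

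The cost is a short wording amendment and one added assay for each participant concerned (at most 18 on the plan's expected numbers). Using the clearance sample needs no further blood draw if its timing is suitable. Dose, infusion schedule, sample size and analysis are unchanged. The article reports 5 participants completed and 1 in treatment out of a planned 30, so at that point most of the planned enrolment could still have been covered.
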